# Effect of a Mediterranean Diet Adapted to the Mexican Population on Indicators of Metabolic Risk in Patients With Obstructive Sleep Apnea: Protocol for a Randomized Controlled Trial

**DOI:** 10.2196/72513

**Published:** 2025-08-21

**Keywords:** obstructive sleep apnea, obesity, hyperglycemia, hypercholesterolemia, Mediterranean diet, nutritional therapy

## Abstract

**Background:**

Obstructive sleep apnea (OSA) is characterized by episodes of intermittent airway obstruction during deep sleep or REM (rapid eye movement). It is associated with cardiometabolic risk diseases. The base treatment is continuous positive airway pressure (CPAP), to which not all patients are able to adapt. The Mediterranean diet (MD) has proven to be effective in reducing cardiovascular risk markers; however, it must be adapted to different populations. Among patients with OSA, it can effectively reduce clinical entity and cardiometabolic risk, while improving quality of life and sleep.

**Objective:**

We aimed to evaluate the effect of an MD adapted to the Mexican diet versus a standard nutritional treatment on metabolic risk indicators in patients with OSA.

**Methods:**

A randomized, 2-arm clinical trial will be conducted with patients with OSA from the Hospital, Mexican Social Security Institute (Instituto Mexicano del Seguro Social) in Mexico. Patients will be randomly included in the group with MD adapted to Mexican foods. With a personalized diet plan adapted from the Mediterranean diet, prototype menus with Mexican foods adapted from the MD will be included for a higher consumption of fruit, vegetables, fiber-rich cereals, and reduction of red meat. In addition to an illustrative plate to improve adherence. The standard diet (SD) group will receive standardized nutritional counseling for patients with OSA. Fasting blood samples will be drawn after 6 and 12 months to identify glucose levels and lipid profiles. Anthropometric and body composition measurements will be taken, and adherence to diet will be recorded after 3, 6, and 12 months. Sleep quality, physical exercise, and life quality will be recorded basally and after 12 months. A multivariate logistic regression analysis will be performed, including the achievement of metabolic indicator control goals, sleep quality, and quality of life as outcome variables. This analysis will be adjusted for other variables that may be statistically significant in the bivariate analysis, such as sex, age, and comorbidities, among others. Statistically significant differences between groups will be considered when the value of *P*<.05.

**Results:**

The protocol was authorized in 2024, and funding is being sought for patient follow-up. All 120 patients (60 per group) will be included in 2025; recruitment will begin in March 2025. The clinical trial is expected to be completed in April 2026.

**Conclusions:**

The results of this study will contribute to evaluate the effect of a nutritional intervention adapted to patients with OSA, seeking to reduce cardiovascular risk indicators in patients, improve their clinical condition, reduce OSA symptoms, and improve patients’ quality of life.

**Trial Registration:**

ClinicalTrials.gov NCT06278571; https://clinicaltrials.gov/study/NCT06278571

**International Registered Report Identifier (IRRID):**

PRR1-10.2196/72513

## Introduction

Obstructive sleep apnea (OSA) is a disease characterized by the partial or total obstruction of airways during sleep [1]. The global prevalence of OSA has been reported to be between 9% and 38%, considering an apnea-hypopnea index (AHI) of ≥5 events per hour; it is higher in men, those with an advanced age, and with urban dwelling [2]. In Mexico, an elevated risk of OSA of 27.3% in adults has been reported, and this risk increases as the BMI is higher. [3]

OSA is estimated to be present in 60% of patients with metabolic syndrome, which can also include, diabetes, obesity, insulin resistance, systemic arterial hypertension, and dyslipidemia [4]. Overweight and obesity contribute to higher amounts of fat in the dilator muscles of neck and tongue, thus increasing OSA. A positive correlation has been found between severe OSA and obesity in adult patients [5].

Daytime symptoms of patients with OSA include excessive daytime drowsiness, complaints of unrefreshing sleep, morning headaches resolved with breathing regulation, irritability, apathy, depression, difficulty to focus, and memory loss, among others [6]. The treatment of choice for patients with OSA, continuous positive airway pressure (CPAP), generates positive air pressure to reduce negative intrathoracic and upper airway pressure, limiting the repetitive hypoxia cycle in the patients; still, adherence is limited [7].

Weight loss in patients with OSA is directly proportional to reduced respiratory events measured by AHI. This was reported in 89 men with OSA who reduced body weight by 7%, fat by 19%, and visceral adipose tissue by 26%, in addition to changes in lifestyle. As a result, OSA was reduced by 15% and 45% of the patients did not need CPAP anymore [8]. Evidence indicates the Mediterranean diet (MD) is widely cardioprotective and contributes to lowering cardiovascular risk and even death [9-11]. The PREDIMED study reported that an MD, mostly consisting of fruit, vegetables, white meat, and dried fruit or olive oil, reduced cardiovascular event symptoms in patients compared to those who followed a controlled diet. The MIMOSA (Mediterranean Diet/Lifestyle Intervention in Obstructive Sleep Apnea) study conducted with 187 adults with OSA showed that an intervention with MD or Mediterranean style had a better effect on improving cardiometabolic indicators than a standard diet (SD) [12]. In addition, the authors report a greater reduction in metabolic syndrome with MD in patients with OSA, even when adjusting fluctuations in body weight as compared with a Mediterranean style or an SD [13,14]. Fewer insomnia episodes have been linked to greater adherence to MD in patients with OSA and insomnia [15]. Although it has been shown to be cardioprotective and improve metabolic indicators, MD must be adapted to other countries. In Mexico, there is scarce evidence on the modification of MD to the Mexican diet and its cardiometabolic effect in patients with OSA. Therefore, the aim of this study is to evaluate the effect of a MD adapted to Mexican eating habits versus a standard nutritional treatment on metabolic risk indicators in patients with OSA.

## Methods

### Study and Population Assignment

A randomized, 2-arm clinical trial will be conducted with patients with OSA from the Regional Hospital, Mexican Social Security Institute (Instituto Mexicano del Seguro Social [IMSS]) in Mexico City with a 12-month follow-up.

The sample size was calculated using the formula for difference in proportions, considering a CI of 95% and a power of 80%. Weight loss is expected in 58% of the sample corresponding to the group given an MD adapted to the Mexican population and in 30% of the group consuming a standard diet, as previously reported in the literature. A sample size of 49 patients per group was obtained and, considering losses of 20%, the total number of patients will be 120 [16].

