### Statistical Analysis

The statistical analysis of the data will be carried out using SPSS (version 27; IBM Corp). The study population will be described using the background, clinical, and pathological variables to characterize the sample of participants with OSA. The Kolmogorov–Smirnov test will be used to identify the distribution of quantitative variables. For variables with normal distribution measures of central tendency and dispersion will be estimated. For variables with a free distribution mean and IQR will be used. Measures of frequency and percentages will be used for sociodemographic and clinical qualitative variables, as well as those of patient proportion with and without glycemic control, and with and without cognitive impairment. A chi-square test will be used to compare the effect of MD versus SD on parameters of control and uncontrol of metabolic risk indicators. Depending on the data distribution, a Student *t* test will be used to compare quantitative variables with parametric distribution between groups, and a Mann-Whitney *U* test will be conducted for free-distribution variables. A multivariate logistic regression analysis will be performed, including the achievement of metabolic indicator control goals, sleep quality, and quality of life as outcome variables. This analysis will be adjusted for other variables that may be statistically significant in the bivariate analysis, such as sex, age, and comorbidities, among others. Statistically significant differences between groups will be considered when the value of *P*<.05.

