### Ethical Considerations

This clinical trial was submitted to the Ethics and Research Committee at HGR 1 “[name] Sánchez Navarrro,” IMSS (registry number R-2024-3609-055). The protocol was reviewed twice for the corresponding modifications related to methodological aspects. The researchers will provide each participant with written consent, describing all the procedures of the clinical trial, the risks, and benefits; this consent form clarifies that the patient is free to not participate or to withdraw from the research without affecting their care at the institution. All participant information collected in the research will be kept confidential, and data will be reported anonymously. Participants in this research will not receive any financial compensation.

The protocol was registered at ClinicalTrials.gov (NCT06782737). The aim of the study, risks, and benefits will be explained in detail to the participants who will freely chose to take part in the trial. They will provide written consent describing each procedure in the trial and respect to information privacy. All the researchers participating receive annual training regarding better clinical practices related to research.

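### The expected 20% loss is met only by recruiting more patients, and the named tests leave out anyone without a 12-month value although 6-month data exist; a baseline-adjusted repeated-measures analysis would use them.

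*Protocol article*

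**What the plan says.** Study and Population Assignment sizes the trial by comparing two proportions, at 95% confidence and 80% power. For the MD arm, "Weight loss is expected in 58% of the sample corresponding to the group given an MD adapted to the Mexican population". The planning rate for the SD arm is 30%. The allowance for loss is stated as follows: "A sample size of 49 patients per group was obtained and, considering losses of 20%, the total number of patients will be 120". The abstract gives 60 per group.

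Statistical Analysis names the comparisons. For goals, "A chi-square test will be used to compare the effect of MD versus SD on parameters of control and uncontrol of metabolic risk indicators". Quantitative variables are compared between groups with a Student t test or, if not normally distributed, a Mann-Whitney test. A logistic regression then takes achievement of goals, sleep quality and quality of life as outcomes. The significance threshold is P<.05. The section gives no repeated-measures method, no baseline adjustment of the quantitative comparisons and no treatment of patients without a final value.

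Table 2 schedules blood pressure, anthropometry and body composition for both arms at baseline, 6 and 12 months. At 3 months the MD arm has these measurements at a visit, while the SD arm has a phone call.

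**The concern.** The trial runs for 12 months and expects to lose one patient in five. Withdrawal is open to every participant ("the patient is free to not participate or to withdraw from the research without affecting their care at the institution"). In a diet trial, patients who are not losing weight may well be those who stop attending. If they leave the analysis, the proportion achieving a goal among those who remain is too high. If they leave at different rates in the two arms, the comparison is distorted as well. Unequal loss is possible here because contact differs by arm at 3 months.

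There is also a cost in information. A patient seen at baseline and 6 months but not at 12 contributes nothing to a 12-month t test or Mann-Whitney test. A t test on final values also makes no use of the baseline measurement of those who complete.

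**Working it through.** **1. The plan's own sample size.** Inputs from Study and Population Assignment: 58% v 30%, 80% power, and 5% significance (from the 95% CI). Two-sided testing is assumed because it reproduces the stated number. With mean rate 0.44:

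n = [1.960·√(2·0.44·0.56) + 0.842·√(0.58·0.42 + 0.30·0.70)]² / 0.28² = (1.376 + 0.567)² / 0.0784 ≈ 48.1, rounded up to **49 per group**. This matches.

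**2. The allowance for loss.** 49 × 1.2 = 58.8, consistent with 60 per group and 120 in total. Expected loss: 0.20 × 120 = 24, or 12 per arm, leaving 48 per arm.

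**3. Effect on power.** For 58% v 30%, the same formula gives:

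| Analysed per arm | Power |
|---|---|
| 48 | 79.9% |
| 49 | 80.7% |
| 60 | 88.0% |

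The stated 80% therefore corresponds to about 48 or 49 analysed per arm. Having one fewer than 49 is immaterial.

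**4. How far the missing 20% could move the result.** Suppose the 48 completers per arm show 58% v 30%. The rate over all 60 is 0.8 × (completer rate) + 0.2 × (rate among the lost).

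| Assumption about the lost | MD | SD | Difference |
|---|---|---|---|
| Same as completers | 58.0% | 30.0% | 28.0 points |
| All fail in both arms | 46.4% | 24.0% | 22.4 points |
| All MD fail, all SD succeed | 46.4% | 44.0% | 2.4 points |
| All MD succeed, all SD fail | 66.4% | 24.0% | 42.4 points |

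The last two rows are logical bounds, not forecasts.

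**5. False-positive rate, as an illustration.** Assume no true effect (30% achieve in each arm, 60 per arm) and that every lost patient is a non-achiever. The completer rate is then 0.30/(1 − loss). Achievers, lost patients and remaining non-achievers were drawn jointly (multinomial) in each arm, and completers were compared by a two-sided chi-square test at 5%.

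| Loss MD/SD | Completer rates | Spurious difference | False-positive rate |
|---|---|---|---|
| 20%/20% | 37.5% v 37.5% | 0 | 5.1% |
| 25%/15% | 40.0% v 35.3% | 4.7 points | about 7.8% |
| 30%/10% | 42.9% v 33.3% | 9.5 points | about 16.3% |

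Only the 20% overall loss comes from the article. The unequal splits and the all-fail assumption are mine.

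**6. With a true effect.** If 58% v 30% holds in all randomised patients and all losses are non-achievers, completers show 0.58/0.8 = 72.5% v 0.30/0.8 = 37.5% at equal 20% loss, which is 35 points instead of 28. At 10%/30% loss they show 64.4% v 42.9%, about 22 points. So equal loss creates no difference from nothing but can stretch a real one, and unequal loss can shift it either way.

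**7. Data available but unused.** By Table 2, weight, waist, body composition and blood pressure exist at 6 months in both arms. For glucose and lipids the article disagrees with itself: Biochemical Indicator Measurement schedules a 6-month sample, but Table 2 shows none.

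**The case against.** The strongest objection is that this is a condensed article. Analysis sets and missing-data rules commonly sit in a full protocol or SAP, and neither is shown. No section says that only patients with a 12-month value are analysed, no time point is attached to the named tests, and raising enrolment for expected loss is ordinary practice. Imputation, or counting losses as failures before a chi-square test, is not excluded. All of this stands, and silence on missing data is not by itself an error here.

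What it does not remove is the choice of method that the article does state. An unadjusted two-group test is fixed for quantitative outcomes in a design that measures both arms at baseline, 6 and 12 months, so an SAP using a repeated-measures model would have to depart from the published section.

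Three stronger readings are tempting and not supported:

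- **That the plan prescribes a completers-only analysis.** This is an inference from the padding and the named tests, not a statement in the article.
- **That loss could by itself produce a difference as large as the 28 points sought.** In the no-effect scenarios above, the largest spurious difference is 9.5 points, and it needs a 30%/10% split with every lost patient failing.
- **That power is really 73%.** Counting losses as failures gives 46.4% v 24.0% and 73.4% power with 60 per arm only if 58% v 30% are completer rates. If they are the rates in all randomised patients and the lost all fail, the same scoring returns 58% v 30% on 60 per arm, with 88.0% power. The article does not say which it means.

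**Conclusion.** The point holds as a weakness of the stated method. Run as written on 12-month outcomes, the tests would rest on about 96 of 120 patients and discard baseline and 6-month data already planned for the rest. The loss of power is negligible. The exposure is bias, and its size depends on assumptions that the article cannot settle. With loss confined to non-achievers and no true effect, the false-positive rate stays near 5% when loss is equal, and rises to about 8% at 25%/15% and 16% at 30%/10%. The different 3-month contact makes unequal loss possible but does not show that it will occur. A better analysis is available at little cost, so the change is worth making before outcomes are analysed.

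**What to change.** In Statistical Analysis:

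- State that all randomised patients are analysed in their assigned group.
- For weight, waist, body composition and blood pressure, replace the t test or Mann-Whitney comparison with a mixed model for repeated measures: baseline as covariate, outcomes at 6 and 12 months, and arm, visit and arm-by-visit terms. The 12-month contrast answers the main question, and a patient lost after month 6 still contributes.
- For achieved/not-achieved goals, use multiple imputation from baseline and available 6-month values, with lost counted as not achieved as a sensitivity analysis. Whether 6-month glucose and lipids are available depends on reconciling Table 2 with Biochemical Indicator Measurement.
- Do not add a 73% power figure to the sample size section, for the reason given under the objection.

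The cost is some extra analysis work in SPSS, which the article already names and which offers mixed models and multiple imputation. No visits or patients are added. Baseline adjustment should also improve precision to the extent that baseline predicts the 12-month value. The price is a missing-at-random assumption in the main analysis, which is why the sensitivity analysis is needed.

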### Selection Criteria

#### Inclusion Criteria

Men and women aged 30-70 years, diagnosed with moderate and severe OSA will be included. Textbox 1 describes the inclusion and exclusion criteria.

Selection criteria for patients with obstructive sleep apnea included in the study.
**Inclusion criteria**
Men and womenAged 30-70 yearsDiagnosed with moderate or severe obstructive sleep apneaUse of continuous positive airway pressure (CPAP)
**Exclusion criteria**
Anatomic alterations of the nose, oropharynx, or maxillaChronic kidney disease under substantive renal function treatmentDecompensated heart failureAny type of cancerNeurological diseaseDiagnosis of depressionRefractory dyslipidemiaFamilial dyslipidemiaSurgeries in the last 6 monthsBMI>40 kg/m²

#### Study Procedures

The study design is a randomized, 2-arm clinical trial in patients with OSA. The patients will be referred by a specialist from the sleep clinic at the Hospital where the study will take place. Once the inclusion criteria are checked, the study, risks, and benefits will be explained to the patients, questions will be answered by the researchers, and the patients will sign informed consent to participate in the trial.

Software will be used for randomization, and patients will be assigned to either of the following groups: MD with Mexican food and SD.

#### Sociodemographic and Clinical Variables

The medical researcher will conduct a clinical interview to obtain sociodemographic data, pathological background, present comorbidities, and current pharmacological treatment.

A medical questionnaire will be applied by the research team to collect sociodemographic data, pathological-clinical background, and nonpathological information. The patients will answer questions regarding age; clinical history, including pathological and nonpathological background; and pharmacological and nonpharmacological treatments.

#### Arterial Blood Pressure Measurement

Arterial blood pressure will be measured by the medical team participating in the study, using a pregauged blood pressure cuff, and no smoking nor consumption of coffee or cola soft drinks in the previous 30 minutes. The patient will sit in a chair, with the back supported and feet straight on the floor. The left arm will be uncovered and supported on a flat table at heart level. The air chamber (balloon) must cover at least three-fourth of the arm’s length and at least 80% of its circumference.

#### Sleep Variable Measurement

During the first consultation at the Sleep Clinic, measurements of AHI and oxygen desaturation index will be recorded using CPAP, as part of the routine studies patients with OSA undergo. The study takes 7-8 hours.

##### Polysomnography

Polysomnography channels will be set up; they include electroencephalographic derivations and electrooculograms, electromyograms of the chin and legs, respiratory flow signals from the thermistor and nasal cannula, respiratory effort signals, continuous oxygen monitoring, electrocardiogram, and the patient’s body position. The study, lasting 4-6 hours, will be carried out once and is part of a series of tests that patients with OSA undergo.

#### Biochemical Indicator Measurement

Venous blood samples will be taken after fasting for 8-10 hours to measure glucose, lipid profile (cholesterol, triglycerides, high-density-lipoprotein cholesterol, and low-density-lipoprotein cholesterol). Measurements will be recorded during the first consultations and after 6 and 12 months.

#### Anthropometric and Body Composition Measurements

Body composition will be measured by bioimpedance, using an InBody 120 composition analyzer, to obtain fat percentage, fat mass, lean mass, and total body water. Body weight and height will be measured with the same analyzer. The patient must wear as little clothing as possible, without any metal objects (bracelets, earrings, rings, belts, and others). The patient will face forward, place their feet on the metal plates, and extend their arms forward to hold the metal bars at a 90º angle. Height will be measured using an InBody ultrasound stadiometer while the patient is in an upright anatomical position. Anthropometry will be recorded by 2 nutritionists previously standardized, using the method proposed by Habitch and according to the specifications previously [17,18]. The BMI will be obtained from height and weight.

Waist circumference will be measured using a measuring tape halfway between the lowest rib and the top of the right hipbone. The average value of the second and third measurements will be used for analysis. Measurements will be taken during the first consultation and after 3, 6, and 12 months.

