**Figure 2 figure2:**
[figure not shown]
Follow-Up and Study Procedures.

Follow-up will continue after 3, 6, and 12 months for MD and 6 and 12 months for SD diet participants, who will attend a consultation with a nutritionist and medical team. In order to measure the adherence to the diet in both groups, the patients will register the 3 days before their clinical visit, 2 registrations from Monday to Friday, and one on weekends. At each visit, nutritional guidelines will be given to improve adherence to the nutritional intervention. The study follow-up is shown in Table 2.

**Table 2 table2:** Study follow-up and procedure in patients with obstructive sleep apnea in both groups.

Time collection	Baseline	3 months	6 months	12 months
Collection of sociodemographic data	MD^a^ and SD^b^	—^c^	—	—
Medical history	MD and SD	—	—	—
Medical evaluation	MD and SD	—	MD and SD	MD and SD
Biochemical data	MD and SD	—	—	MD and SD
Arterial blood pressure and Anthropometric and body composition measurements	MD and SD	MD	MD and SD	MD and SD
Sleepiness with Epworth sleepiness scale	MD and SD	MD and SD	MD and SD	MD and SD
Quality of life with Quebec Sleep Questionnaire (QSQ)	MD and SD	—	—	MD and SD
Physical activity with IPAQ^d^ Questionnaire	MD and SD	—	MD and SD	MD and SD
Adherence to the diet intervention with records of the previous 3 days	MD and SD	MD	MD and SD	MD and SD
Adherence to the diet intervention with MEDAS^e^ Questionnaire	MD and SD	MD	MD and SD	MD and SD
Phone call follow-up	—	SD	—	—

^a^MD: Mediterranean diet.

^b^SD: standard diet.

^c^Not applicable.

^d^IPAQ: International Physical Activity Questionnaire.

^e^MEDAS: 14-point Mediterranean diet adherence screener questionnaire.

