### Primary Outcomes

The primary objective of this clinical trial is to evaluate the effect of the MD adapted to the Mexican diet versus an SD treatment on metabolic risk indicators in patients with OSA (body weight, fasting glucose, lipid profile, WC, and body composition).

The secondary outcomes are to evaluate the effect of the intervention on:

Sleep quality through ESS.Changes in quality of life through QSQ.Adherence to nutritional therapy intervention through records of meals corresponding to previous and MEDAS questionnaires.

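### Waist circumference, a primary indicator, is taped by study nutritionists under a visit schedule that lets the measurer know the arm, so it carries an avoidable risk of observer bias

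*Protocol article*

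**What the plan says.** The Primary Outcomes section lists the primary metabolic risk indicators as "body weight, fasting glucose, lipid profile, WC, and body composition", so waist (WC) is one of them.

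Under Anthropometric and Body Composition Measurements, weight and body composition come from a bioimpedance analyzer. Waist does not: "Waist circumference will be measured using a measuring tape halfway between the lowest rib and the top of the right hipbone". On who measures, the section says "Anthropometry will be recorded by 2 nutritionists previously standardized". On repeat readings it says "The average value of the second and third measurements will be used for analysis", and on timing "Measurements will be taken during the first consultation and after 3, 6, and 12 months", with no limit to one arm.

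Under Follow-Up and Study Procedures, the visits differ by arm: "Follow-up will continue after 3, 6, and 12 months for MD and 6 and 12 months for SD diet participants". These are the patients "who will attend a consultation with a nutritionist and medical team", and "At each visit, nutritional guidelines will be given to improve adherence to the nutritional intervention". Table 2 places blood pressure, anthropometry and body composition at 3 months in the Mediterranean diet arm only. The standard diet arm has a phone call at that time. At 6 and 12 months, anthropometry, the 3-day diet record and the diet adherence questionnaire are scheduled together in both arms.

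**The concern.** Of the indicators in the Primary Outcomes section, waist depends most on the person taking it, through tape position and tension. The analyzer and laboratory values leave much less room for this.

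As described, the measurer can know the arm in two ways. First, the reading belongs to a visit at which diet is discussed and guidance is given. Second, under Table 2 only Mediterranean diet patients are measured at 3 months. A nutritionist who measured a patient then knows the arm when measuring that patient again at 6 and 12 months. The second route holds even if measuring and counselling are done by different people.

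The article also states its expectation openly: the Results and Anticipated Findings sections look for better indicators under the Mediterranean diet. A shared expectation of that kind can shift readings in one direction. Such a shift would pass straight into the between-group difference, and none of the tests named under Statistical Analysis (t test, Mann-Whitney, chi-square, logistic regression) can take it out again.

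**Working it through.** **1. Which safeguards act on which error.**

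- Standardizing the two nutritionists reduces differences between observers.
- The fixed landmark reduces variation in where the tape goes.
- Averaging the second and third readings reduces random reading error.
- None of these acts on a shift that follows the arm, because that shift is common to repeat readings and can be common to both observers.

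The article mentions no masking of the measurer. The limitations it lists (adherence, CPAP use, self-reported sleep quality, single center) do not include unmasked measurement.

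**2. Sample size, to fix the number analyzed.** The article gives 49 per group for 58% versus 30%, two-sided 5% (assumed) and 80% power. With pooled variance and mean proportion 0.44:

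n = [1.96·√(2·0.44·0.56) + 0.842·√(0.58·0.42 + 0.30·0.70)]² / 0.28² = (1.376 + 0.567)² / 0.0784 ≈ 48.1, rounded up to 49.

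This reproduces the stated figure. It concerns weight loss, not waist. With 60 enrolled per group and 20% losses, 60 × 0.8 = 48 per group remain.

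**3. Illustration of size.** The article gives neither a standard deviation for waist nor a size of observer bias, so both are assumptions. Let s be the standard deviation, b the arm-related reading difference, and the true effect zero.

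SE = s·√(2/48) = 0.2041·s

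False-positive rate = P(Z > 1.96 − b/SE) + P(Z < −1.96 − b/SE)

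| Quantity tested | s (cm) | SE (cm) | b = 1 cm | b = 2 cm |
|---|---|---|---|---|
| Raw 12-month waist | 12 | 2.45 | 6.9% | 12.9% |
| Change in waist | 8 | 1.63 | 9.4% | 23.2% |
| Change in waist | 6 | 1.22 | 12.9% | 37.2% |
| Change in waist | 5 | 1.02 | 16.5% | 50.0% |

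Example, first row with b = 1: b/SE = 0.408, so the rate is P(Z > 1.552) + P(Z < −2.368) = 0.060 + 0.009 = 0.069.

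The raw-value row is closest to the text, because Statistical Analysis compares quantitative variables between groups and does not mention change scores.

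**4. Control versus no control.** Statistical Analysis also compares proportions in control. With s = 12 cm and the cut at the mean, where reclassification is greatest, a 1 cm shift moves Φ(1/12) − 0.5 = 3.3% of patients across the cut, and a 2 cm shift moves Φ(2/12) − 0.5 = 6.6%.

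**5. More patients do not help.** With 60 analyzed per group and s = 12 cm, the rates for 1 and 2 cm are 7.4% and 15.0%, slightly higher than with 48.

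**6. The 3-month schedule.** The Anthropometric section gives a 3-month measurement without naming an arm, and so does the abstract. Table 2 gives it to the Mediterranean diet arm only. The two cannot both describe the procedure. Disclosure of the arm through the schedule follows from the Table 2 version.

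**The case against.** The strongest reply is that this is an inference from silence in a condensed article. One section names two nutritionists who record anthropometry, and another names a nutritionist and the medical team at the consultation. Nothing says that these are the same people. The sentence on guidance is passive and names no giver. Who stands where during a visit is the sort of detail a full protocol may settle, and the SPIRIT appendix is not shown.

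Much of this stands. A reader might infer that the person whose counselling is being judged also holds the tape. The documents do not support that, and the point does not need it. What remains is what the article does set out: the tool, the measurers, the visits, the safeguards and a schedule that measures one arm only at 3 months. That schedule can disclose the arm whoever does the counselling.

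A second reply is that the landmark is fixed, the observers are standardized and the readings are averaged, which leaves little room for a 1 to 2 cm shift. It is fair that these narrow observer discretion and that nothing in the article supports a bias of that size. They still do not hide the arm.

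A third is that the larger percentages need a change-score analysis that the article does not describe. That is correct, and those figures should be read as conditional.

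A fourth is reach: waist is one of several primary indicators, the others come from an instrument or a laboratory, and the sample size rests on weight loss. That also stands, and it limits the point to waist.

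**Conclusion.** The concern holds as a risk of observer bias in one primary indicator. The procedure as described lets the measurer know the arm, and the stated safeguards act on random error, not on an arm-related shift.

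If that shift were 1 to 2 cm, the false-positive rate for waist would be about 7% to 13% instead of 5% on raw 12-month values, or about 13% to 37% if change scores were tested. These figures assume 48 per group, no true effect, and standard deviations of 12 cm and 6 cm respectively. None of the standard deviations or bias sizes comes from the article.

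The documents do not show that bias will occur, and they give no reason to doubt the analyzer or laboratory outcomes on this ground. The change is worth making because it is cheap and protects a primary outcome, not because the design is invalid without it.

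**What to change.** Add to Anthropometric and Body Composition Measurements: the 6- and 12-month waist readings are taken before the consultation by whichever of the two nutritionists does not counsel that patient and did not see them at 3 months, without sight of the allocation or of earlier values. Both nutritionists are already standardized, so either can measure. If in practice neither one counsels, the sentence still needs the 3-month and order-of-visit conditions.

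Reconcile that section and the abstract with Table 2 on which arm is measured at 3 months.

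For readings where this was not done, report waist as unmasked and interpret it with that caution. The analyzer's fat mass and fat percentage can be shown beside it as a supporting check. They are whole-body measures and cannot stand in for central fatness.

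The cost is one sentence and some rostering so that the right nutritionist is available at the 6- and 12-month visits. No added staff, procedures or patients are needed. Patients may occasionally reveal their arm, so the change reduces the risk without removing it.
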